### Primary outcome

The primary outcome parameter is the ED risk status as metrically measured by the Ch-EDE-Q global mean score six months after participation in the prevention program. This would correspond Ch-EDE-Q global mean score differences between intervention and control group of 0.34 for female as well as 0.18 for male participants; based on the expected effect size of Cohen’s d = 0.3 and standard deviations of 1.14 (females) and 0.61 (males) within comparable population based samples [54].

### Secondary outcome

Knowledge about EDs, internalization of Western beauty ideals, body dissatisfaction, self-concept as well as symptoms of depression and anxiety are considered to be secondary outcomes.

### Study hypotheses

It is hypothesized that the prevention program reduces the individual ED risk in participants of the intervention group compared to the control group. It is also expected that, participants of prevention program have increased knowledge about EDs, decreased body dissatisfaction and symptoms of depression as well as anxiety compared to the control group.

### Handling of missing values

Participants with missing baseline ChEDE-Q global score will need to be excluded from the analysis. With the aim to include a maximum of participants in the analysis each questionnaire set will be labeled regarding group and sex. Information about these independent variables can, therefore, be derived if at least one questionnaire is answered. Also, information regarding the independent variables grade and type of school can be gathered from the documentation of the recruitment process.

### Statistical analyses

In order to empirically test the hypotheses regarding differences between the intervention and control groups at the 6-month follow-up, multi-level analyses are conducted with school as a random factor as well as sex (male vs. female), grade (8th vs. 11th), parents’ educational level (lower- both parents vs. higher – one parent vs. higher both parents) and group (intervention vs. control) as fixed factors and baseline ChEDE-Q scores as covariate. Two-sided tests with an alpha level of p < .05 and regression coefficients with 95% confidence intervals (CI) are calculated in all analyses. Analyses are first performed on completers and then sensitivity analyses are conducted using imputed data.

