## Methods

### Study design

A cluster-randomized controlled trial was designed to evaluate the efficacy of the prevention program. To this end, global ED risk, and knowledge about EDs as well as values of different ED risk factors are measured one month before, immediately following, as well as six months after the intervention in both conditions of the trial.

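### The single 6-month model names baseline ChEDE-Q as its only baseline score; read literally, the secondary outcomes are not adjusted for their own baselines, which costs precision

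*Protocol article*

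**What the plan says.** The protocol article describes one model. Under Statistical analyses it is introduced as follows: "In order to empirically test the hypotheses regarding differences between the intervention and control groups at the 6-month follow-up, multi-level analyses are conducted". School is the random factor; sex, grade, parents' education and group enter "as fixed factors and baseline ChEDE-Q scores as covariate". The same section adds: "Two-sided tests with an alpha level of p < .05 and regression coefficients with 95% confidence intervals (CI) are calculated in all analyses".

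Study hypotheses goes beyond eating disorder risk. Its further expectation reads: "participants of prevention program have increased knowledge about EDs, decreased body dissatisfaction and symptoms of depression as well as anxiety compared to the control group". Secondary outcome gives the full list: "Knowledge about EDs, internalization of Western beauty ideals, body dissatisfaction, self-concept as well as symptoms of depression and anxiety are considered to be secondary outcomes".

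The baselines of these measures exist. According to Study design, "global ED risk, and knowledge about EDs as well as values of different ED risk factors are measured one month before, immediately following" and again at six months. Variables and instruments confirms that both arms complete the same questionnaire set at equal intervals.

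Handling of missing values ties exclusion to one baseline score only, the ChEDE-Q global score.

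**The concern.** The model is introduced for hypotheses in the plural, and four of those concern measures other than the ChEDE-Q. No separate model and no other baseline covariate appears for any secondary outcome. Taken at its word, the plan adjusts a 20-item knowledge score, the PHQ-9 and the GAD-7 for baseline eating pathology and ignores baseline knowledge, depression and anxiety.

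An outcome's own baseline is usually its best available predictor. Leaving it out leaves residual variance that could have been removed, and a chance difference between arms on that measure is corrected only as far as ChEDE-Q happens to track it. Schools are randomised, and the registered title speaks of 20 of them, so chance differences are not negligible.

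The missing-data rule has a related effect: a pupil with complete PHQ-9 data would drop out of the depression analysis because a different questionnaire was missing at baseline.

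**Working it through.** **1. Which outcomes the covariate fits**

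| Outcome | Named in Study hypotheses | Measured at baseline | Own baseline in the model |
|---|---|---|---|
| ChEDE-Q global score (primary) | yes | yes | yes |
| Knowledge | yes | yes | no |
| Body dissatisfaction (KEDS) | yes | yes | no |
| Depression (PHQ-9) | yes | yes | no |
| Anxiety (GAD-7) | yes | yes | no |
| Internalization (SATAQ-G) | no, but secondary outcome | yes | no |
| Self-concept (MSWS) | no, but secondary outcome | yes | no |

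**2. The plan's own clustering figures**

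Sample size/power calculation uses an intra-cluster correlation of 0.05 and 65 participants per cluster. The design factor is 1 + (65 − 1) × 0.05 = 4.2, and 352 × 4.2 = 1478.4, which reproduces the stated 1478. The present point does not alter these figures. They are used below, on the assumption that the same intra-cluster correlation applies to the secondary outcomes.

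**3. Loss of precision**

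The documents give no correlation between follow-up and baseline scores. Assumed: 0.5 to 0.7 with the own baseline (r_own), and 0.2 to 0.4 with baseline ChEDE-Q (r_C).

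In SD units the variance of a school mean is 0.05 + 0.95/65 = 0.0646, of which 0.05/0.0646 = 77% lies between schools. The gain from adjustment therefore depends mainly on how far the covariate explains school differences, which the documents do not tell. Two cases:

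- Case A, adjustment removes only within-school variance: V(r) = 0.05 + 0.95 × (1 − r²)/65.
- Case B, the same correlation holds between and within schools: V(r) = 0.0646 × (1 − r²).

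The standard error with ChEDE-Q as covariate, relative to the own baseline, is √[V(r_C)/V(r_own)].

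| r_own | r_C | Case A variance ratio | Case A SE ratio | Case B variance ratio | Case B SE ratio |
|---|---|---|---|---|---|
| 0.5 | 0.4 | 0.06228/0.06096 = 1.022 | 1.011 | 0.84/0.75 = 1.12 | 1.058 |
| 0.7 | 0.2 | 0.06403/0.05745 = 1.114 | 1.056 | 0.96/0.51 = 1.882 | 1.372 |

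So the excess is about 1% to 6% in case A and 6% to 37% in case B. If r_own and r_C were both 0.4, there would be no loss in either case. A school-level correlation above the pupil-level one would give more than case B. The calculation ignores sex, grade and parental education, which are already in the model.

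**4. Chance imbalance**

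With 1478 analysed, the standard error of a baseline difference between arms is √(4 × 4.2/1478) = 0.107 SD, and 1.96 × 0.107 = 0.21 SD. Suppose an outcome's own baseline differs by 0.1 SD, ChEDE-Q is balanced, and ChEDE-Q relates to the outcome only through that baseline. Then 0.1 × r_own = 0.05 to 0.07 SD stays in the estimate, if the slope is the same between schools. This is the loss of step 3 seen in a single realised trial, not a second loss on top of it.

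**The case against.** The strongest reply is that the sentence was written for the primary outcome, where baseline ChEDE-Q is the own baseline, and is shorthand elsewhere. The section is visibly not exhaustive: Handling of missing values treats type of school as an independent variable, yet the model omits it, and the high-risk hypothesis in the Discussion has no model. The exclusion rule fits a description of the primary analysis alone just as well. A condensed article may also leave secondary covariates to a fuller document.

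This lowers confidence in what was intended, but nothing in the article states the shorthand. The article does name a covariate and attaches it to hypotheses that include secondary outcomes. If another covariate was meant, the wording still needs changing.

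The reply is also right on size. Three stronger inferences are tempting, and the documents do not support them:

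- **Biased secondary results.** Randomisation keeps the estimate unbiased in expectation without the own baseline, and the model's standard error already allows for chance imbalance. Principals do nominate classes after learning the allocation (Recruitment), so systematic imbalance is conceivable. That is a separate design question, and the article does not show that it occurred.
- **An uncorrected 0.13 SD against a planned effect of 0.3.** This figure takes 20 schools of 65, an imbalance of 1.96 standard errors, a correlation of 0.6 and no correction through ChEDE-Q: 1.96 × √(4 × 4.2/1300) × 0.6 = 0.13. It is an extreme case, and d = 0.3 is tied to the ChEDE-Q under Primary outcome; no effect is planned for the secondary outcomes.
- **A threefold variance for depression.** This would rest on the PHQ-9 retest reliability of 0.84, whose interval the article does not give. It is no estimate of a six-month correlation.

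**Conclusion.** The point holds for the secondary outcomes only. As worded, the plan uses a covariate suited to the primary outcome for every 6-month comparison and leaves unused the baselines it collects. The consequence is a less precise secondary analysis, not an invalid one. The primary analysis and the sample size are untouched.

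The loss cannot be given as one figure. The two ranges, about 1% to 6% and 6% to 37% in standard error, rest on assumed correlations and differ only in whether the covariate explains between-school variance. A reader might take 37% as the expected loss; it is the top of the second range and requires the most favourable pupil-level correlations to hold at school level as well. Because the better covariates are already collected, the change is worth making even at the lower end. It is a free improvement.

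**What to change.** In Statistical analyses, state that each outcome is adjusted for its own baseline value: ChEDE-Q for the primary outcome, and the respective baseline score for knowledge, SATAQ-G, KEDS, MSWS, PHQ-9 and GAD-7. Baseline ChEDE-Q may be kept as an additional covariate for the secondary outcomes.

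In Handling of missing values, confine the ChEDE-Q exclusion rule to the primary analysis, so that a missing baseline ChEDE-Q does not by itself remove a participant from a secondary analysis. If ChEDE-Q is kept as an additional covariate, say how its missing values are handled there; the plan already foresees imputed data for sensitivity analyses.

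The cost is a sentence in each section. No new data are needed and the sample size does not change. The choice should be fixed before outcome data are compared by arm.

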### Sample size/power calculation

Participants are adolescents of grades 8 and 11 (age 14 and 17 years). Based on previous studies [46] an effect size of Cohen’s d = 0.3 is expected. For a two-sided test with a type-I error rate of 5% and power of 80%, two samples with 176 participants each (N = 352) are needed to reach statistical significance. Given that cluster effects, expected inter-class correlations of 0.05 as well as an average cluster size of 65 participants need to be considered, the design factor is 4.2. Thereby at least 1478 participants need to be recruited. If an additional drop-out-rate of 25% is assumed then a total of 1848 participants are needed to be recruited.

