### Methods to reduce bias

Selection bias is minimized by the inclusion of a control group as well as the externally conducted cluster randomization of participating schools. The rate of participants or their parent who refrain from signing an informed consent (i.e. nonresponse rate) will be reported. The full recruitment process will be documented according to CONSORT reporting standards [54]. Surveys with high possibility of intentional misrepresentation (e.g. always choosing the one option of the likert scale) are considered as having dropped out. In addition, data is subjected to an internal validity check.

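### The main analysis rests on completers and bars pupils without a baseline ChEDE-Q score although imputation is already planned; at the plan's 25% drop-out, about 462 of 1848 enrolled pupils are left out

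*Protocol article*

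**What the plan says.** Two rules in the protocol article decide which pupils enter the main analysis.

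- Statistical analyses fixes the order: "Analyses are first performed on completers and then sensitivity analyses are conducted using imputed data". The model is multilevel, with school as a random factor; sex, grade, parental education and group as fixed factors; and "baseline ChEDE-Q scores as covariate".
- Handling of missing values removes a further set: "Participants with missing baseline ChEDE-Q global score will need to be excluded from the analysis". The sentence does not say whether it applies to the completer analysis only or to the imputed analysis as well.

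The same section then sets out to keep as many participants as possible in the analysis. It explains how other variables can be recovered: "each questionnaire set will be labeled regarding group and sex", and "information regarding the independent variables grade and type of school can be gathered from the documentation of the recruitment process".

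The expected loss is stated under Sample size/power calculation: "If an additional drop-out-rate of 25% is assumed then a total of 1848 participants are needed to be recruited".

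Two further facts bear on the point. Under Recruitment, schools are the unit of randomisation, principals are told their arm, and only then are classes nominated. Under Study design, both arms are measured before the intervention, immediately after it and at six months.

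**The concern.** The article expects to lose a quarter of its pupils, plans imputation, and then takes the main result from the pupils who were not lost. Three things make this a weak choice.

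1. A completer analysis with this model is valid only if loss is unrelated to the six-month score given baseline score, sex, grade, parental education and group. A pupil whose eating pathology worsened between baseline and the post-intervention questionnaire, and who then missed follow-up, breaks that condition. The worsening is on record for such a pupil, but the completer model does not use it.
2. Excluding pupils without a baseline score discards any later scores they have. The school knows its arm by the time baseline is taken, so the exclusion follows allocation, and the share excluded could differ between arms.
3. The baseline rule works against the aim stated in its own section, and the exclusion is not necessary. A missing baseline covariate can be imputed, and imputation is already in the plan.

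What is at stake is the credibility of the headline contrast at six months, which would describe a selected subset rather than the pupils enrolled in each arm.

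**Working it through.** **Inputs** (protocol article, Sample size/power calculation): 176 pupils per arm, 352 in total; intra-cluster correlation 0.05; average cluster size 65; drop-out 25%; total to recruit 1848.

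**Reproducing the plan's figure**
- Design factor: 1 + (65 − 1) × 0.05 = 4.2
- Before drop-out: 352 × 4.2 = 1478.4, stated as 1478
- With drop-out: 352 × 4.2 × 1.25 = 1848, as stated

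**Size of the completer restriction**
- Left out at 25%: 0.25 × 1848 = 462
- Analysed: 1848 − 462 = 1386

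The plan reached 1848 by adding 25% to 1478. That margin is 1848 − 1478 = 370 pupils, or 370 / 1848 = 20.0% of those recruited. How the total was inflated is a separate matter. The figure of 462 takes the stated 25% rate at face value.

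**If missing baseline scores come on top**

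The article gives no rate for these and does not say whether they fall inside the 25%. The rates below are assumptions, applied to the 1386 who remain.

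| Missing baseline (assumed) | Analysed | Share of 1848 left out |
|---|---|---|
| 0% | 1386 | 25.0% |
| 2% | 1386 × 0.98 = 1358 | 1 − 0.75 × 0.98 = 26.5% |
| 5% | 1386 × 0.95 = 1317 | 1 − 0.75 × 0.95 = 28.8% |
| 10% | 1386 × 0.90 = 1247 | 1 − 0.75 × 0.90 = 32.5% |

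Parental education is a factor in the model but is not among the variables described as recoverable. Gaps in it could also remove pupils from a completer model. No rate is given, so this is not counted.

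**Order of events** (Recruitment; Study design)
1. Schools are randomised.
2. Principals are told the arm.
3. Principals nominate classes.
4. Consent letters go out.
5. Pupils in those classes complete the baseline questionnaire.

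Whether a baseline score exists is therefore settled after allocation is known to the school.

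**What the model uses against what is collected**
- The model for the six-month score uses the baseline score and the fixed factors listed above.
- The immediate post-intervention score is collected in both arms and is not in that model. It should not be added as a covariate, because it lies on the path from programme to outcome.
- It can properly be used as a predictor in an imputation model or as one of the responses in a three-wave model. There it informs the missing six-month value without adjusting away the effect.

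**The case against.** The strongest reply is that the plan already contains the remedy. The imputed analysis is prespecified, so a reader will see both results and can compare them. In addition, a completer mixed model adjusted for baseline is valid when loss depends only on its covariates, and imputing the outcome from those same covariates would add little. Both statements are correct. They leave two gaps. The headline result would still come from completers. And as worded, the baseline exclusion may carry into the imputed analysis, which would then not cover all pupils either. The gain from changing the order comes from the post-intervention score and from the later scores of pupils without a baseline.

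The article does not describe the imputation model, and it may well use the post-intervention score. That detail may properly be left to a fuller document and is not held against the plan.

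A reader might infer more than the documents support:

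- **More than a quarter of randomised pupils are lost.** Schools are randomised, not pupils, and the stated rate is 25%. Anything above that needs baseline or covariate losses outside the 25%, which no section states.
- **A clear loss of power.** Such a calculation would hold the design factor at 4.2 while pupils are lost. If schools stay and 65 falls to 65 × 0.75 = 48.75, the factor becomes 1 + (48.75 − 1) × 0.05 = 3.39. Power is not the argument here.
- **A bias of known size.** The article gives neither drop-out by arm nor scores of drop-outs. An unadjusted illustration would also ignore the planned covariates.
- **Symptom-free pupils removed by the survey screen, by assessors who know the arm.** Under Methods to reduce bias, surveys likely to be misrepresented "are considered as having dropped out", and one-option answering is given as an example. Nothing says that lowest answers on the ChEDE-Q alone trigger removal, or who does the screening and what they see.

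**Conclusion.** The point holds as a weakness in two stated rules that should be changed. On the plan's own 25% drop-out, 462 of 1848 enrolled pupils are outside the main analysis. The number is larger only if missing baseline scores are additional to that rate.

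The exclusion for a missing baseline is made after schools know their arm and is not confined to one analysis. It also runs against the section's own aim of keeping participants in.

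The direction and size of any bias cannot be derived from the article. If loss depends only on the model's covariates, the completer result is not biased by it. The conclusion rests on reading the analysis performed first as the main one, and on 25% being a share of those recruited.

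**What to change.** - Make the primary analysis cover all enrolled pupils, in the arm to which their school was allocated. Use multilevel multiple imputation that respects clustering by school and includes the baseline, post-intervention and six-month ChEDE-Q scores. An equivalent three-wave mixed model would also serve, provided baseline enters as a response so that pupils without it still contribute.
- Replace the exclusion under Handling of missing values with imputation of the missing baseline score.
- Report the completer analysis as the sensitivity analysis.

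The three waves of data and the imputation are already planned, so the cost is revised wording and a little more analysis work. The downside is that the main result then relies on a missing-at-random imputation model, which the completer analysis would sit beside as a check.

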### Methods to reduce bias

Selection bias is minimized by the inclusion of a control group as well as the externally conducted cluster randomization of participating schools. The rate of participants or their parent who refrain from signing an informed consent (i.e. nonresponse rate) will be reported. The full recruitment process will be documented according to CONSORT reporting standards [54]. Surveys with high possibility of intentional misrepresentation (e.g. always choosing the one option of the likert scale) are considered as having dropped out. In addition, data is subjected to an internal validity check.

### Study registration

Before starting, the trial was registered with an internet-based open access trial, controlled-trails.com (ISRCTN97989348; “Healthcare Network Anorexia and Bulimia nervosa”-campaign - Focal-project 1: Prevention trial at 20 secondary schools in Hamburg; Principal Investigator: [name]; Registered 19 December 2012; Overall trial status: Ongoing; Recruitment status: No longer recruiting).

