#### Recruitment

All secondary school principals within the Metropolitan area of Hamburg are informed about the study purpose and procedure by letters and emails. Participating schools are randomized into the study condition (intervention vs. control) according to the order of application. Randomization is carried out by an external institution (Department of Medical Biometry and Epidemiology, University Medical Center Hamburg-Eppendorf). It is important to note that we were prevented from randomizing according to classes as well as classes switching study condition (e.g. intervention vs. control at the beginning of a new school year) by the Hamburg supervisory school authority. Schools are, therefore, the unit of randomization and they stay in the same condition for the entire study duration.

After randomization school principals are informed to which study condition their school is allocated (intervention vs. control) as well as the detailed study procedure. School principals then nominate suitable classes and propose convenient time slots in the school year. Teachers of participating classes are provided with a detailed schedule of the study and are also given the chance to contact the research team at any time. A letter of consent with study information is distributed to students and their parents two weeks before the study is conducted. These letters contain a detailed description of the study procedure (especially the necessity of randomization). Classes randomized to the control group are given the opportunity to receive the intervention after the completion of the last questionnaire. Study participants have the possibility to contact a psychotherapist from the research team to seek professional mental health help throughout the whole study duration.

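### The sample size (65 per cluster, design factor 4.2, 1848 recruited) does not fit the only school count given, 20; if 20 is the plan, unadjusted power is below the stated 80%

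*Protocol article*

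**What the plan says.** All of this is in the protocol article.

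- **Recruitment** fixes the cluster: "Schools are, therefore, the unit of randomization and they stay in the same condition for the entire study duration". Randomizing by class was ruled out by the school authority.
- **Statistical analyses** agrees: school is the random factor, and the baseline ChEDE-Q score is a covariate.
- **Sample size/power calculation** starts from "an effect size of Cohen’s d = 0.3 is expected", two-sided 5% and 80% power, so that "two samples with 176 participants each (N = 352) are needed to reach statistical significance". It then allows for clustering: "expected inter-class correlations of 0.05 as well as an average cluster size of 65 participants need to be considered", with a design factor of 4.2. This gives 1478, raised to 1848 for 25% drop-out. The Abstract repeats 1848. The section gives no number of schools.
- **Study registration** has the only school count in the article, inside the registered title: "Focal-project 1: Prevention trial at 20 secondary schools in Hamburg".

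**The concern.** In a school-randomized trial, power depends mainly on the number of schools. Once schools are as large as these, extra pupils per school add little. The sample size section never uses that number, and the one number printed elsewhere does not multiply out to its totals. A reader cannot tell which design was powered: about 28 schools of 65, or 20 larger schools.

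The stated 80% is what readers would use to interpret a null result on the primary outcome. If the trial was planned with 20 schools, that figure is too high under the section's own assumptions.

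**Working it through.** **Inputs.** d = 0.3, two-sided 5%, 80% power, 176 per arm, ICC 0.05, cluster size 65, design factor 4.2, 1478, 25% drop-out, 1848 (Sample size/power calculation); 20 schools (Study registration); cluster = school (Recruitment, Statistical analyses).

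**1. The plan's own figures.**
- A two-sample t-test with d = 0.3 needs 175.4 per arm, rounded up to 176, so N = 352.
- Design factor = 1 + (m - 1) x ICC = 1 + 64 x 0.05 = 4.2.
- 352 x 4.2 = 1478.4, stated as 1478.
- 1478 x 1.25 = 1847.5, stated as 1848.

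The chain reproduces. (A 25% loss from 1848 leaves 1386, not 1478. That is a separate matter, but it decides which analysed number applies below.)

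**2. Can 20, 65 and 1848 all hold?**
- 65 enrolled per school: 20 x 65 = 1300, below both 1478 and 1848.
- 65 analysed per school: enrolment would be 1300 x 1.25 = 1625, or 1300 / 0.75 = 1733. Neither is 1848.
- 1848 from 20 schools: 1848 / 20 = 92.4 enrolled, or 1386 / 20 = 69.3 analysed. Neither is 65.
- Schools needed at 65 each: 1478 / 65 = 22.7, so 23; 1848 / 65 = 28.4, so 28 to 29.

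No reading makes the three agree.

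**3. Unadjusted power if there are 20 schools.** With k schools and m analysed per school, N = k x m, DE = 1 + (m - 1) x 0.05, effective N = N / DE, and the non-centrality is 0.3 / sqrt(4 / effective N). Power is taken from the normal approximation and from a non-central t with k - 2 = 18 df. Equal arms and equal school sizes are assumed.

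| Analysed (per school) | DE | Effective N | Normal | t, 18 df |
|---|---|---|---|---|
| 1300 (65) | 4.20 | 309.5 | 75.1% | 70.4% |
| 1386 (69.3): 1848 less 25% | 4.42 | 313.9 | 75.7% | 71.0% |
| 1478 (73.9) | 4.65 | 318.2 | 76.3% | 71.6% |
| 1848 (92.4): no loss | 5.57 | 331.8 | 78.0% | 73.4% |

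Worked line for 1386: DE = 1 + 68.3 x 0.05 = 4.415; 1386 / 4.415 = 313.9; non-centrality = 0.3 / sqrt(4 / 313.9) = 2.66.

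Adding pupils helps slowly. Effective N cannot exceed 20 / 0.05 = 400, and reaching 80% by the normal approximation would take about 130 analysed per school, or 2600 in total.

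**4. What could close the gap.**
- *Baseline covariate.* The article gives no correlation for this purpose. As an assumption, take r = 0.24 to 0.44, the retest range quoted for the Ch-EDE-Q, and replace d by 0.3 / sqrt(1 - r²). This supposes that the covariate reduces between-school and within-school variance equally. With 1386 analysed in 20 schools, power is 78% to 84% (normal) or 74% to 80% (t, 18 df).
- *More schools.* With 28 schools and 65 x 0.75 = 48.75 analysed in each, DE = 3.39, effective N = 403, and power is 85% (normal) or 83% (t, 26 df).
- *Lower ICC.* At 0.04 instead of the stated 0.05, the 1386 case gives 82% or 78%.

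**The case against.** The strongest reply is that 20 appears once, inside a registered title, and nowhere in the design, recruitment or sample size sections. Recruitment describes an invitation to all secondary school principals in the area, with no cap. The sample size section is coherent in itself and implies about 28 schools at enrolment, which would more than deliver 80%. This stands in part. The shortfall is conditional on 20 being the planned number, and the article does not settle that. The mismatch itself is not conditional: the title is printed as this trial's registration, and nothing explains the difference.

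Second, about half of the gap to 71% comes from using 18 df. The choice of denominator degrees of freedom is commonly left to the analysis plan, and the article says nothing wrong about it. This stands. By the normal approximation alone the gap is 4 to 5 points with 1300 to 1478 analysed, and 2 points with no loss.

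Third, the planned analysis adjusts for baseline, so an unadjusted figure understates its power. This also stands, but the stated 80% takes no credit for the adjustment and gives no correlation to support any.

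A reader might infer that the trial's power simply is 71%, or that the design factor of 4.2 is an error. The documents support neither. The first needs 20 schools, 18 df and no covariate, all at once. The second overlooks that 4.2 is correct for an average of 65; moving to 69.3 changes it only to 4.4 and power by less than one point.

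**Conclusion.** The inconsistency is established from the article's own numbers: 65 per school and a total of 1478 or 1848 do not fit 20 schools. The power consequence is conditional. If 20 schools were planned, then with ICC 0.05, d = 0.3, equal arms and no covariate, the recruited 1848 with 25% loss gives about 76% (normal) or 71% (t, 18 df). None of the unadjusted 20-school cases in the table reaches 80%. If about 28 schools were planned, the 80% is met. No bias or invalid estimate follows, because the planned model includes school as a random factor. What needs correcting is the stated basis of the power claim.

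**What to change.** In Sample size/power calculation:

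1. State the planned number of schools per arm and the expected number of pupils enrolled and analysed per school, and show how these give the 1848.
2. Restate the design factor and power for that number of schools, preferably with between-school degrees of freedom. With 20 schools and 25% loss, the design factor is about 4.4.
3. If credit is taken for the baseline covariate, state the assumed correlation and label it as an assumption.
4. If 20 was not the planned number, say so beside the registered title in Study registration and give the number that was.

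The cost is a recalculation and a few sentences. No extra recruitment is needed. If 20 is confirmed, the price is a less favourable stated power.
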